### Interim analyses {21b}

No interim analyses are planned.

### Methods for additional analyses (e.g. subgroup analyses) {20b}

A sensitivity analysis will be done for the primary endpoint adjusted for smoking during pregnancy and any breastfeeding during the stay in the hospital. No further subgroup analyses are planned.

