**Methods:**

Preterm infants with a gestational age between 25 weeks + 0 days and 28 weeks + 6 days who are breathing spontaneously on continuous positive airway pressure with supplemental oxygen at or below 30% in the first hour of life will be randomised to a prophylactic LISA treatment with 100–200 mg surfactant intratracheally per kilogramme bodyweight (intervention group) or will continue the continuous positive airway pressure treatment (control group). Participants will have follow-up until age 5 years. At that time, the children will be tested by spirometry, and forced expiratory volume within 1-s *z*-scores will be compared between the intervention and control groups as the primary outcome parameter of the trial. Secondary endpoints include additional lung function parameters, endurance, motor development, intelligence, and sensitivity for infectious lung diseases. Short-term safety assessment will be done after completed enrolment (*n* = 698) and discharge of all infants. This safety assessment will include in-hospital mortality and short-term complications.

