## Introduction

### Background and rationale {6a}

Less invasive surfactant administration (LISA) describes intratracheal surfactant administration via a small diameter tube to spontaneously breathing infants [1]. The current guidelines recommend surfactant therapy in preterm infants if the fraction of inspired oxygen (FiO_2_) is higher than 0.30 and LISA as the optimal mode of administration for preterm infants on continuous positive airway pressure (CPAP) [2]. This recommendation is based on a number of randomised controlled trials and meta-analyses [3–7]. The use of prophylactic LISA in infants with FiO_2_ at or below 0.30 was not yet tested in randomised controlled trials.

Observational data from the GNN indicate that in infants with gestational age 25–28 weeks and FiO_2_ ≤ 0.30, LISA treatment rates are as high as 50%. Reasons for this high rate of LISA despite the lack of data and high costs of surfactant therapy are unclear.

Prophylactic surfactant therapy via an endotracheal tube is not superior to early CPAP and selective surfactant treatment of infants requiring intubation [8]. Furthermore, even LISA causes some stress for preterm infants, since the trachea is intubated with a small diameter tube, which can induce discomfort, coughing, desaturations, tracheal obstruction, and bradycardia. Possible benefits of LISA prophylaxis include a lower rate of intubation and mechanical ventilation and better long-term lung function [9]. The existing uncertainties concerning LISA prophylaxis prompted us to design and initiate the pro.LISA trial.

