#### Criteria for discontinuing or modifying allocated interventions {11b}

The intervention (prophylactic surfactant) will be applied immediately after enrolment. No criteria for modifications were defined.

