### Sample size {14}

The clinical aim is to detect a mean difference in FEV_1_
*z*-scores of 0.3 at the age of 5 years [9]. Based on the values of the GNN study, the *z*-score standard deviation is expected to be 1.07. The significance level alpha is set to 0.05 (two-sided) and power to 0.8. To detect this effect using a two-sample *t*-test, it requires data from 201 patients per group. The total sample size is calculated on the following assumptions: adjustment for multiple births (10%), rate of patients dying before discharge (2%), loss to follow-up rate (28%), and the rate of patients who will not be able to accomplish lung function tests at the age of 5 years (10%). Based on these estimates, we calculated that data from 349 patients per group are needed (698 patients in total, nQuery 7.0).

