### Assignment of interventions: allocation

#### Sequence generation {16a}

A stratified permuted block randomisation is used with stratification by gestational age (25 and 26 weeks vs. 27 and 28 weeks), multiple birth status, and participating study centres. The randomisation lists are prepared by the Institute of Medical Biometry and Statistics.

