### Assignment of interventions: blinding

#### Who will be blinded {17a}

Blinding of physicians and nurses for the intervention is not possible in this study. Parents and outcome assessors of the primary outcome at age 5 years will be blinded to the procedure.

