## Statistical methods

### Statistical methods for primary and secondary outcomes {20a}

All details of statistical analyses will be specified in the statistical analysis plan, which will be finalised before the inclusion of the last patient. The primary and other efficacy endpoints will be analysed in the full analysis population. Patients who died before the 5-year follow-up and patients who were not able to complete the lung function test will be excluded from the full analysis set. The primary endpoint will be tested in a generalised estimating equation model assuming Gaussian error and exchangeable correlation matrix using a two-sided Wald test at a significance level alpha of 0.05.

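### The adjusted sensitivity analysis of FEV1 conditions on breastfeeding in hospital, which is observed after randomisation and could be affected by allocation

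*Protocol article*

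**What the plan says.** The section on additional analyses {20b} of the protocol article plans one sensitivity analysis of the primary endpoint, "adjusted for smoking during pregnancy and any breastfeeding during the stay in the hospital". It gives no reason for choosing these two covariates and no caveat about either.

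The timing is clear. According to the Abstract, eligible infants "in the first hour of life will be randomised to a prophylactic LISA treatment". The eligibility criteria {10} require an age below 60 minutes, and the participant timeline {13} places allocation in the same window. Section {11b} adds: "The intervention (prophylactic surfactant) will be applied immediately after enrolment".

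The primary endpoint, the FEV1 z-score at 5 years, is to be "tested in a generalised estimating equation model assuming Gaussian error and exchangeable correlation matrix using a two-sided Wald test" (section {20a}). That section names no covariates and leaves the details to the statistical analysis plan. Randomisation uses "stratification by gestational age (25 and 26 weeks vs. 27 and 28 weeks), multiple birth status, and participating study centres" (section {16a}).

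**The concern.** The two covariates are of different kinds. Smoking in pregnancy is settled before allocation. Breastfeeding during the stay unfolds over the weeks after the infant has been allocated and treated.

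The article itself gives a reason to think allocation could change the course of those weeks: "Possible benefits of LISA prophylaxis include a lower rate of intubation and mechanical ventilation and better long-term lung function" (section {6a}). The dissemination section {31a} also allows that short-term complications may differ between the arms. The further step, from an easier or harder respiratory course to more or less breastfeeding, is an assumption; the documents do not state it. Staff behaviour is a second possible route, since "Blinding of physicians and nurses for the intervention is not possible in this study" (section {17a}).

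If allocation does affect breastfeeding, adjusting for it does two things:

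- It removes whatever part of the effect runs through breastfeeding.
- It opens a path through causes that breastfeeding and FEV1 share, such as how ill the infant was or family background.

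The coefficient is then not the total effect of allocation. Without strong assumptions it is not a clean direct effect either. A sensitivity analysis should ask the same question under different assumptions, and this one may ask a different question. What is at stake is its value as support for the primary result.

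**Working it through.** **1. The plan's own figures.** Inputs from section {14}: difference 0.3 z, SD 1.07, two-sided alpha 0.05, power 0.80. For a two-sample t-test with the noncentral t distribution, power is 0.7987 at 200 per group and 0.8007 at 201, so 201 is reproduced. Inflation for multiple births (10%), death (2%), loss to follow-up (28%) and inability to perform spirometry (10%):

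201 × 1.10 / (0.98 × 0.72 × 0.90) = 221.1 / 0.63504 = 348.2, rounded up to 349 per group, 698 in total.

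Breastfeeding enters none of these inputs, so nothing below changes them.

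**2. Order of events.**

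| Variable | Fixed when | Before randomisation? |
|---|---|---|
| Smoking in pregnancy | before birth | yes |
| Gestational age group, multiple birth, centre | at or before birth | yes |
| Allocation and surfactant | before 60 min of age | – |
| Any breastfeeding during the stay | between treatment and discharge | no |

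**3. How far adjustment moves the estimate.** In a linear model fitted to the same children, with breastfeeding as the added covariate,

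adjusted − unadjusted = −(p1 − p0) × b,

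where p1 and p0 are the breastfeeding proportions in the intervention and control arms and b is the fitted breastfeeding coefficient within arms. The identity is exact for least squares and serves as an approximation for the GEE. Because b is the fitted coefficient, it contains both a causal effect of breastfeeding and any association due to shared causes.

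**4. Numbers.** The documents give neither p1 − p0 nor b. Both are assumptions.

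| p1 − p0 | b (z) | Size of shift (z) | Share of 0.3 z target |
|---|---|---|---|
| 0 | any | 0 | 0% |
| 0.10 | 0.3 | 0.10 × 0.3 = 0.03 | 10% |
| 0.15 | 0.5 | 0.15 × 0.5 = 0.075 | 25% |

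The sign depends on the signs of p1 − p0 and b, and the documents settle neither.

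**5. Simulation check.** Two million infants were simulated per scenario. Assumed values: 70% breastfed in the control arm; treatment effect not through breastfeeding 0.30 z; where a shared cause is present, it is worth 0.5 z per SD on FEV1 and correlates 0.5 with the underlying tendency to be breastfed. Entries are adjusted minus unadjusted, in z.

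| Allocation raises breastfeeding by | Mediator only (0.3 z effect) | Shared cause only | Both |
|---|---|---|---|
| 0 points | 0.00 | 0.00 | 0.00 |
| 5 points | −0.015 | −0.021 | −0.036 |
| 10 points | −0.030 | −0.042 | −0.072 |
| 15 points | −0.045 | −0.065 | −0.110 |

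These agree with step 3. At 10 points, for example, the mediator-only shift is 0.10 × 0.3 = 0.03. The meaning differs by column. In the first, the shift is the gap between a total and a direct effect. In the second, breastfeeding has no effect on FEV1, so the shift is pure bias.

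**6. Scale.** With 201 per group, the standard error of the difference is 1.07 × √(2/201) = 0.107 z. Shifts of 0.03 and 0.075 z are about 0.3 and 0.7 of a standard error. The largest simulated shift, 0.110 z, is about one.

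**The case against.** The strongest reply is that no decision rests on this analysis. It is labelled a sensitivity analysis, the confirmatory test is the GEE Wald test, and efficacy is also to be examined in other analysis populations, including per protocol. That stands. A reader might infer that the primary result itself is biased; the documents do not support this, because breastfeeding is not named in the primary model.

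Second, a reader might infer that this is the only covariate-adjusted analysis in the whole plan. The article cannot establish that. It defers details to a statistical analysis plan that is not shown, and the GEE may include the stratification factors. The statement holds only for what the article describes.

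Third, the effect on breastfeeding may be small or absent. Parents are blinded, the covariate is the coarse any-versus-none, and about half of the controls are expected to receive LISA within 3 days (section {6b}). The assumed associations of 0.3 and 0.5 z are as large as or larger than the trial's target effect. Section {6a} names intubation, ventilation and lung function as possible benefits; it does not claim an effect on NEC surgery or length of stay. All of this is fair, and it is why the range must start at zero.

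Fourth, a disagreement with the primary result would not be uninterpretable. The illustrated shifts of 0.03 and 0.075 z are below one standard error, and breastfeeding rates by arm would help to read them. That too stands.

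What remains is the covariate itself. The article states it affirmatively, so the point does not depend on anything left to the statistical analysis plan.

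**Conclusion.** The point holds in a limited form. The one adjusted analysis of FEV1 that the article describes conditions on a variable observed after randomisation and treatment. If allocation changes breastfeeding, the estimate ceases to target the total effect of allocation and may carry bias from shared causes. Its agreement or disagreement with the primary result then says less about robustness than it should.

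The size is not known. It is zero if the arms do not differ in breastfeeding, and 0.03 to 0.075 z (10% to 25% of the target) under the two assumed combinations in step 4. The bias is possible, not shown: the documents contain no breastfeeding rate, no effect of LISA on breastfeeding and no breastfeeding–FEV1 association.

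The primary test, alpha, power, and the 201 and 349 per group are unaffected. It would also go too far to say that the sensitivity analysis is worthless; it is weakened, and avoidably so.

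**What to change.** Remove breastfeeding from the adjusted sensitivity model and restrict that model to variables fixed before randomisation: smoking in pregnancy, optionally with the stratification factors (gestational age group, multiple birth status, centre). Sex need not be added for this purpose, since the z-score already standardises for it.

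Report any breastfeeding by arm descriptively. If breastfeeding is of interest as a pathway, use it only in a separate analysis labelled exploratory mediation, with its assumptions stated.

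The cost is a one-line change in section {20b} and the matching line of the statistical analysis plan, made before the 5-year data are analysed. It needs no new data collection and no change to the sample size.

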### Methods in analysis to handle protocol non-adherence and any statistical methods to handle missing data {20c}

The primary and secondary endpoints can only be examined if the patients are able to conduct the tests. Patients who are not able to conduct the tests and patients who died before the assessment will be excluded from the full analysis set.

Other scenarios for not conducting a follow-up are the following: unattainability of a patient, absence at the follow-up appointment, or the parents do not want to attend the follow-up examination. For these scenarios, missing values might not be related to the outcome and be comparable to the observed values in the intervention and control groups, and these scenarios assume that values are missing at random or missing completely at random. Thus, a multiple imputation for the endpoints will be done.

No other imputations of missing data will be performed, and all other analyses will be based on complete cases.

### Plans to give access to the full protocol, participant-level data, and statistical code {31c}

After analysis and publication of the primary and secondary outcome data, full access to de-identified patient-level outcome data, the full protocol of the trial, and the statistical code will be available upon reasonable request.

### Oversight and monitoring

#### Composition of the coordinating centre and trial steering committee {5d}

The trial management group includes the principal investigator, clinical and administrative research associates, research nurses, data managers, and statisticians. The trial management group has weekly meetings. Reports concerning site-specific enrolment numbers are provided to participating sites and the data and safety monitoring board every month. Personnel meetings of the whole study group are scheduled every 6 months.

#### Composition of the data monitoring committee, its role, and reporting structure {21a}

The data and safety monitoring board include an independent statistician, a clinical expert in neonatology, and two representatives of preterm infant parent organisations. The role of the data and safety monitoring board is to monitor the progress of the trial and to ensure that the conduct of the trial is safe and ethically acceptable. The data and safety monitoring board reports to the sponsor/investigator who has full responsibility regarding any decision concerning the continuation or stopping of the trial.

#### Adverse event reporting and harms {22}

Preterm infants are a vulnerable group of patients and a high number of adverse events was anticipated in the pro.LISA trial. Typical complications of preterm birth (e.g. intraventricular haemorrhage, surgery due to necrotising enterocolitis) were defined as adverse events, are collected systematically, and are entered in the pro.LISA online database. Serious adverse events (deaths in particular) are reported to the principal investigator within 24 h either by fax or in the pro.LISA online database. Unexpected harms will be also collected as adverse events or serious adverse events in the online database. Harms will not be classified according to standardised classifications like the “common terminology criteria for adverse events”. Suspected unexpected serious adverse reactions are not expected since more than a million preterm infants have already been treated with surfactant. Suspected unexpected serious adverse reactions will be reported to the principal investigator within 24 h.

Descriptive analyses of adverse events and serious adverse events including IVH, PVL, surgery for PDA, surgery for NEC, surgery for FIP, surgery for ROP, and pneumothorax are provided every month to the data and safety monitoring board and participating sites.

#### Frequency and plans for auditing trial conduct {23}

Trial institutions, facilities, and all data on electronic case record forms must always be available for inspection by an authority. Online monitoring of electronic case record forms is done by the trial management group on a continuous basis. Close out of centres after completed enrolment will be done by personnel visits.

#### Plans for communicating important protocol amendments to relevant parties (e.g. trial participants, ethical committees) {25}

Changes and additions to the protocol will be submitted to the ethics committees of all participating centres and regulators for review and approval. Thereafter, changes are communicated to participating sites and—if necessary—to parents of trial participants.

#### Dissemination plans {31a}

In general, results from the study will only be published after the database has been closed. Exceptions are publications concerning the design of the study and descriptive results of safety analysis after discharge from the hospital of all enrolled infants. The latter is planned, since the primary endpoint will be measured 5 years after discharge of the last enrolled patient. Since short-term complications might be different between the groups, we are planning descriptive outcome analyses of these data after enrolment is completed.

The final report of the trial will be published within a period of 360 days upon completion of the study.

## Discussion

In meta-analyses of randomised controlled trials, surfactant application via LISA is superior to surfactant application via an endotracheal tube in terms of mechanical ventilation within the first 72 h of life, BPD, other complications of preterm birth, and mortality [7]. Furthermore, LISA is now recommended as the preferred mode of surfactant administration in preterm infants with FiO_2_ > 30% [2].

Important uncertainties persist with regard to the possible benefits of LISA in preterm infants with mild respiratory distress syndrome and FiO_2_ ≤ 0.30. Furthermore, studies targeting long-term outcomes of preterm infants who were treated with LISA have not been performed yet.

Prophylactic LISA treatment rates will be 100% in the intervention group of the pro.LISA trial and 0% in the control group. We estimated that within the first 3 days of life, about 50% of control group infants will develop FiO_2_ exceeding 0.30 and will receive LISA. If a similar rate of additional LISA treatment is necessary in the control group will be analysed in the pro.LISA trial. Furthermore, the pro.LISA trial will provide important information if the short-term benefits of prophylactic LISA treatment do exceed the undeniable additional stresses, discomforts, and costs that are induced by a prophylactic LISA procedure. Even if there are no differences with regard to short-term safety data, prophylactic LISA might improve long-term lung function. This endpoint is the target of the primary long-term efficacy endpoint of the pro.LISA trial.

## Trial status

The current protocol version number is Pro.LISA_01_31 version 4 from 11 January 2023. The pro.LISA trial started enrolment in February 2022. The approximate date when recruitment will be completed is the year 2024.

## Abbreviations

BMBF: German Federal Ministry of Education and Research
CPAP: Continuous positive airway pressure
EFCNI: European Foundation for the Care of Newborn Infants
FEV_1_: Forced expiratory volume within 1 s
FiO_2_: Fraction of inspired oxygen
FVC: Forced vital capacity
GNN: German Neonatal Network
LISA: Less invasive surfactant administration
UKSH: University Hospital of Schleswig–Holstein
WPPSI: Wechsler Preschool and Primary Scale of Intelligence
